## Abstract

**Background:**

Post‐stroke cognitive impairment (PSCI) is a common complication following stroke, with limited effective treatments. This randomized controlled trial aims to evaluate the efficacy of two non‐pharmacological interventions—electroacupuncture therapy (EA) and herbal olfactory therapy (HOT)—in improving cognitive function in PSCI patients, both as standalone treatments and in combination.

**Methods:**

This parallel‐group, assessor‐blinded, randomized controlled trial will recruit 210 PSCI patients, randomly assigned to one of six groups: control, EA, HOT, combination therapy, sham therapy, or the healthy (ratio 1:1:1:1:1:1). All participants will receive standard cognitive training and basic medical care. The EA group will receive 4 weeks of electro‐acupuncture at specific acupoints. The HOT group will receive 4 weeks of aromatic inhalation therapy using Acorus tatarinowii volatile oil. The combination group will receive both interventions. The primary outcome measure is cognitive function, assessed using the Montreal cognitive assessment (MoCA) at baseline, week 4, and week 8. Secondary outcomes include the mini‐mental state examination (MMSE), functional magnetic resonance imaging (fMRI), near‐infrared spectroscopy (fNIRS), and anxiety assessment using the state‐trait anxiety inventory (STAI) at baseline and week 4. Data analysis will be conducted using a modified intention‐to‐treat approach.

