**FIGURE 1 brb370631-fig-0001:**
[figure not shown]
Flow diagram of the study.

The sample size for this study will be calculated using the formula for a superiority trial of two independent sample sizes. Clinical experience and preliminary research indicated an effective rate of 90% in the treatment group and 80% in the control group (Hei et al. 2023, Su et al. 2023, Zhang et al. 2023). Based on these data, we conducted a sample size calculation using a two‐tailed *t*‐test with the following parameters: test boundary value *δ* = 0.15, significance level *α* = 0.025, and power *β* = 0.20 (Zabor et al. 2020). The calculation was performed using the following formula.

$$n=\left[{\left(Z_{\alpha /2}+Z\beta \right)}^{\wedge 2}*\left(p1\left(1-p1\right)+p2\left(1-p2\right)\right)\right]/{\left(\delta -|p1-p2|\right)}^{\wedge 2}$$

Considering a case number ratio of k = 1 between groups, the calculated sample size was 32 cases per group. To account for a potential 10% dropout rate, we increased the sample size to approximately 35 cases per group (International Council for Harmonisation of Technical Requirements for Pharmaceuticals for Human Use 1998). The total sample will be divided into 6 groups: control, EA, HOT, combination therapy, sham therapy, or the healthy, totaling around 210 cases to be included.

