### Randomization and Blinding

2.4

Using a random number table method, the PSCI participants in the trial will be randomly allocated to (1) the control group, (2) the EA group, (3) the HOT group, (4) the combination group, (5) the sham group, and (6) the healthy group, with 35 individuals in each group. Notably, the present study was designed as a separate cohort of healthy subjects to assess brain functional abnormalities in patients with PSCI using functional magnetic resonance imaging (fMRI) and to validate the effects of interventions such as acupuncture and ATR volatile oil therapy on brain function. Data from healthy people provide a baseline of normal brain function for the study, helping to identify pathological changes in stroke patients. The allocation process is concealed, and the assessors will be kept blinded to the participant's allocation. Participants are instructed not to discuss their research participation or experiences with the assessors during the evaluation period. Patients will be informed that they would receive either EA treatment, HOT, or both, without being informed about the number of acupoints or the specific stimulation sites.

Acupuncture and herbal treatments will be administered by licensed acupuncturists, while a qualified rehabilitation physician will train a research assessor to evaluate the efficacy of acupuncture. The research assessor and data analysts will remain blinded to group assignment, although participants will be informed during the informed consent process.

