#### Generation of Random Allocation Sequence

2.5.1

Use of randomization tools: A random number table or equivalent randomization tool was employed to generate a numerical randomization sequence.Group assignment: Each random number was uniquely mapped to a participant ID and subsequently designated as either the experimental group or control group. This process was exclusively conducted and documented by authorized personnel.

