### Data Analysis

2.11

Researchers who are blind to the groupings will conduct data management and statistical analysis on the data acquired using the statistical software SPSS 22.0 (SPSS Inc., Chicago, IL, United States). Descriptive statistics will be utilized to depict the baseline characteristics of the two participant groups, with mean ± standard deviation for normally distributed continuous data and median and quartiles for non‐normally distributed continuous data. The normality of the data will be assessed using the Shapiro–Wilk test, and the homogeneity of variance will be assessed using the Levene test. One‐way analysis of variance (ANOVA) will be used for comparisons among multiple groups for normally distributed continuous data, while repeated measures analysis of variance will be used for within‐group pre‐ and post‐treatment comparisons. The Kruskal–Wallis test will be employed for non‐normally distributed continuous data. The significance level (α) for the statistical hypothesis tests will be set at *p* < 0.05, one‐tailed.

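### The healthy cohort is counted as one of six randomised arms: randomised patients number 175, not 210, and the multi-group tests are not limited to the randomised arms

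*Protocol article*

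**What the plan says.** **Who is randomised.** The Abstract (Methods) states that the trial "will recruit 210 PSCI patients, randomly assigned to one of six groups: control, EA, HOT, combination therapy, sham therapy, or the healthy", in a ratio of 1:1:1:1:1:1. Section 2.4 repeats this: "the PSCI participants in the trial will be randomly allocated to (1) the control group", and the list ends with "6) the healthy group, with 35 individuals in each group". Section 2.1 reports that "the calculated sample size was 32 cases per group", raises this to about 35 for dropout, and divides a total of around 210 over the same six groups.

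**The contrary statement.** The next sentence of section 2.4 says "the present study was designed as a separate cohort of healthy subjects to assess brain functional abnormalities in patients with PSCI" by fMRI. It goes on to say that the cohort also serves to validate the effects of the interventions on brain function.

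**Eligibility.** Section 2.2 asks for stroke, a PSCI diagnosis, an MMSE below an education-specific cut-off (17, 20 or 24) and 3 to 6 months since the stroke, together with age, consent and general criteria.

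**Allocation list.** Section 2.5.1 says each random number is "subsequently designated as either the experimental group or control group".

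**What the healthy group receives.** Section 2.6.5 gives healthy participants an olfactory treatment and refers for the procedure to section 2.6.1, which is the control group's section.

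**Analysis.** In section 2.11, one-way ANOVA "will be used for comparisons among multiple groups for normally distributed continuous data", with Kruskal-Wallis for non-normal data. The groups entering the test are not named, and the same section speaks of two participant groups when describing baseline data.

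**The concern.** The text gives two incompatible accounts of the healthy group: a randomised arm of PSCI patients, and a cohort recruited apart from them. Only the second is possible. This has three consequences.

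- The headline sample size counts people who are not patients and are not randomised.
- A healthy-versus-patient comparison is presented as if randomisation protected it, which it cannot.
- The six groups are the fullest set the article defines, so a test among multiple groups can be read as including the healthy. Section 2.2 selects patients for low cognition. A six-group test on raw MoCA scores could then be significant because of the disease alone, and would say nothing about treatment.

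**Working it through.** **1. The count.** Inputs: 32 per group before dropout, 35 after, six groups, total 210 (section 2.1).

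- Plan's figure: 32 x 1.10 = 35.2, taken as 35; 6 x 35 = 210. It reproduces, but only with the healthy group included.
- Groups to which a patient can be randomised: control, EA, HOT, combination, sham. 5 x 35 = 175.
- Overstatement: 210/175 = 1.20, that is 20%. Put the other way, 35/210 = 16.7% of the stated patients are not patients.

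This step needs no assumption beyond the article's own group size. The per-group 32 is taken as given; whether it follows from the printed formula is a separate matter.

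**2. Six-group ANOVA on raw scores when no treatment works.** Inputs: k = 6 groups, n = 32 per group, level 0.05 (section 2.11). The article gives no MoCA mean or SD, so the gap d between healthy participants and patients, in SD units, is an assumption and a range is shown.

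With five equal patient arms and one group shifted by d, the noncentrality is

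lambda = n x (5/6) x d² = 32 x 0.8333 x d² = 26.67 d²,

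with 5 and 6 x 32 - 6 = 186 degrees of freedom.

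| Gap d (SD, assumed) | lambda | Rejection rate, n = 32 | Rejection rate, n = 35 |
|---|---|---|---|
| 0 | 0 | 5% | 5% |
| 0.25 | 1.67 | 13.4% | 14.3% |
| 0.5 | 6.67 | 46.5% | 50.7% |
| 0.75 | 15.0 | 85.5% | 88.9% |
| 1.0 | 26.67 | 98.8% | 99.3% |
| 1.5 | 60.0 | >99.9% | >99.9% |

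**3. Simulation check.** 1,000 runs per setting, 35 per group, assumed gaps of 3, 5 and 8 MoCA points and SDs of 3, 4 and 5. The six-group ANOVA rejected in 70% to 100% of runs and Kruskal-Wallis in 67% to 100%. With the healthy group removed, the five-arm ANOVA rejected in 3.7% to 5.7%, close to the nominal 5%.

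**4. The same test on change from baseline.** What matters here is how differently the healthy change. With 35 per group and an assumed SD of change of 3 points, the rejection rate is 5% if patients and healthy participants change equally, 23% if their mean changes differ by 1 point, and 79% if they differ by 2.

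**The case against.** The best defence is that section 2.4 shows the intended role of the healthy group, so a reader can work out that five arms are randomised. Section 2.11 does not say that all six groups enter the MoCA test, nor whether raw or change scores are used. Membership of each test is also commonly settled in an analysis plan, which is not shown here.

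Much of this stands. A reader might infer that the MoCA omnibus test would be significant even if no treatment works. The article does not support that as a flat statement: it follows only if the healthy group enters and raw scores are tested, and its size rests on an assumed gap. Nor would an omnibus rejection driven by healthy participants by itself yield a false claim that combination beats monotherapy, which is the stated aim.

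Three further inferences also go too far:

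- Not every inclusion criterion requires a stroke; age, consent and the mental-health criterion do not. It is the criteria taken together that exclude healthy people, and separate volunteer criteria may sit in the full protocol.
- Section 2.4 does not confine the cohort to a reference role, since it also mentions validating intervention effects.
- The two-group wording in section 2.5.1 may be generic. It does not show that the actual allocation list is wrong.

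The defence does not remove the contradiction or the miscount. The separate-cohort sentence conflicts with the allocation text beside it and does not correct the Abstract or section 2.1.

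**Conclusion.** The point holds in two parts of different strength.

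**Firm:** the Abstract and sections 2.1 and 2.4 count the healthy group among randomised PSCI patients, and section 2.4 contradicts this. On the article's own group size, 175 patients are randomised and the stated 210 is 20% too high. This takes the sham group as a real arm, as the Abstract and sections 2.1, 2.4 and 2.6.6 do.

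**Conditional:** section 2.11 does not limit the multi-group tests to the randomised arms. If all six groups enter on raw scores, the false-positive rate for treatment at 32 per group runs from about 13% at a gap of 0.25 SD to over 99.9% at 1.5 SD. The MMSE entry cut-offs make a large MoCA gap plausible, but the article does not quantify one. On change scores the inflation may be nil or substantial.

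Section 2.6.5 adds an unresolved conflict: a cohort meant to show normal brain function is given an olfactory treatment and referred to the control group's procedure.

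**What to change.** 1. In the Abstract and sections 2.1 and 2.4, state that 175 PSCI patients are randomised 1:1:1:1:1 to control, EA, HOT, combination and sham, and that 35 healthy volunteers are recruited separately and are not randomised.
2. In section 2.2, say that the listed criteria apply to patients and that the volunteers have their own.
3. In section 2.5.1, describe the allocation list as five-arm, and confirm that the list in use matches.
4. In section 2.11, restrict the efficacy tests (MoCA, MMSE, MBI, STAI) to the five randomised arms. Use the healthy cohort only in an imaging comparison labelled as non-randomised.
5. Reconcile section 2.6.5 with the reference role in section 2.4. Section 2.6.6 defines the sham arm's other treatments by pointing to 2.6.5, so this wording also affects a randomised arm.

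The cost is rewording plus a check of the allocation list. No extra patients or assessments are needed.

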**Aims:**

This study aims to evaluate the clinical efficacy of EA at cervical acupoints combined with HOT for PSCI, with a specific focus on determining the therapeutic superiority of this combined approach over monotherapy interventions.

## Introduction

1

In recent years, the global incidence, disability rate, and recurrence rate of stroke have remained high (GBD 2019 Stroke Collaborators 2021). Research data from various hospitals in China indicates that around 2 million people experience new‐onset strokes in the country annually (Wang et al. 2022). Stroke can result in neurological functional abnormalities, leading to cognitive, speech, physical, swallowing, and daily life functional impairments. Post‐stroke cognitive impairment (PSCI) is a clinical syndrome characterized by cognitive impairments persisting for up to 6 months after a stroke, with main clinical manifestations including varying degrees of impairment in attention, memory, orientation, perception, and executive function (Verdelho et al. 2021). The incidence of PSCI in stroke patients ranges from 17% to 92%, with 6% to 32% potentially progressing to dementia (Filler et al. 2024, Pendlebury and Rothwell 2009, Mahon et al. 2017). While medications for treating PSCI may offer some improvement in cognitive function, they also come with significant adverse effects (Shen et al. 2022). Consequently, the search for effective treatment strategies for post‐stroke cognitive impairment has become a key focus of research both domestically and internationally.

Traditional Chinese medicine treatment has been gaining attention, with aromatic opening drugs known for their strong, pleasant aroma and efficacy in treating conditions like central nervous system disease (Hou et al. 2021). Acorus Tatarinowii (ATR) contains various chemical components, including volatile oils, organic acids, terpenes, flavonoids, and amino acids. Despite volatile oils making up a small percentage (0.11‐0.42%) of ATR's composition, they are considered the key components for their pharmacological effects. Studies conducted in vitro and in vivo have highlighted the pharmacological activity of the active ingredients β‐asarone and α‐asarone in ATR's volatile oil, particularly in neurodegenerative diseases. These compounds have shown the ability to cross the blood‐brain barrier and exert rapid effects (Wang et al. 2023, Ning et al. 2024, Chellian et al. 2017).

Modern pharmacological studies have shown that ATR can protect central neurons, enhance memory and learning functions, resist nerve cell apoptosis, and inhibit central cholinergic activity, leading to significant therapeutic effects (Wang et al. 2023, Xu et al. 2023). Herbal olfactory therapy (HOT) using traditional Chinese medicinal materials triggers biochemical reactions in the respiratory, nervous, and circulatory systems, influencing human emotions, physiology, and behavior (Zhang et al. 2021). The volatile oil of ATR can quickly penetrate the blood‐brain barrier to provide therapeutic benefits. Moreover, certain acupuncture points have been found to stimulate brain activity and cognitive function. For example, Suliao (GV25) is known for its ability to clear heat and improve mental clarity, while Yingxiang (LI20) can enhance energy flow and cognitive function. By applying essential oils to these specific acupoints, the absorption of the oils can be enhanced, leading to improved therapeutic outcomes.

Electroacupuncture therapy (EA) involves connecting an electroacupuncture device to acupoints in the neck area and has been used in the clinical treatment of cerebral ischemia with significant therapeutic effects. [name] proposed a novel treatment method for cerebrovascular diseases, which includes needling the bilateral Fengchi (GB20) and Gongxue to stimulate them with pulsed electric currents (Liu et al. 2017). This stimulation improves inadequate cerebral blood supply and enhances cerebral blood circulation. Electroacupuncture connecting the Fengchi (GB20) and Gongxue has shown noticeable effects in promoting meridian function, regulating metabolism, and improving limb and language functions in patients with head and neck diseases such as brainstem ischemia (Fu et al. 2023, Wang et al. 2009). This study aims to evaluate the clinical efficacy of electroacupuncture combined with ATR volatile oil inhalation therapy in treating PSCI. The research seeks to provide evidence that the integration of EA with ATR volatile oil inhalation therapy offers superior clinical benefits compared to single‐modality treatments for PSCI, through rigorous clinical investigation.

## Methods

2

### Objectives and Sample Size

2.1

This randomized controlled trial with 6 groups of therapists, assessors, and participants will be conducted from April 2024 to April 2025 in the Department of Rehabilitation Medicine at the Affiliated People's Hospital of Hangzhou Medical College. The study involves a 4‐week intervention for the enrolled patients. The study protocol was approved by the Institutional Review Board of the Affiliated People's Hospital of Hangzhou Medical College and was registered at https://register/clinicaltrials.gov(NCT06313866). Voluntary written informed consent will be obtained from all participants before entering the trial. We reported the trial according to the Consolidated Standards of Reporting Trials (CONSORT) statement (Figure 1).

**FIGURE 1 brb370631-fig-0001:**
[figure not shown]
Flow diagram of the study.

The sample size for this study will be calculated using the formula for a superiority trial of two independent sample sizes. Clinical experience and preliminary research indicated an effective rate of 90% in the treatment group and 80% in the control group (Hei et al. 2023, Su et al. 2023, Zhang et al. 2023). Based on these data, we conducted a sample size calculation using a two‐tailed *t*‐test with the following parameters: test boundary value *δ* = 0.15, significance level *α* = 0.025, and power *β* = 0.20 (Zabor et al. 2020). The calculation was performed using the following formula.

$$n=\left[{\left(Z_{\alpha /2}+Z\beta \right)}^{\wedge 2}*\left(p1\left(1-p1\right)+p2\left(1-p2\right)\right)\right]/{\left(\delta -|p1-p2|\right)}^{\wedge 2}$$

Considering a case number ratio of k = 1 between groups, the calculated sample size was 32 cases per group. To account for a potential 10% dropout rate, we increased the sample size to approximately 35 cases per group (International Council for Harmonisation of Technical Requirements for Pharmaceuticals for Human Use 1998). The total sample will be divided into 6 groups: control, EA, HOT, combination therapy, sham therapy, or the healthy, totaling around 210 cases to be included.

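### Section 2.1 claims a superiority sample size with a 15-point boundary but assumes only a 10-point benefit; the stated 32 per group matches a non-inferiority calculation instead

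*Protocol article*

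**What the plan says.** Section 2.1 (Objectives and Sample Size) says the size is "calculated using the formula for a superiority trial of two independent sample sizes". On the planning rates it says "Clinical experience and preliminary research indicated an effective rate of 90% in the treatment group and 80% in the control group". The remaining inputs are a "two‐tailed *t*‐test with the following parameters", then "test boundary value *δ* = 0.15", "significance level *α* = 0.025" and "power *β* = 0.20" (read here as 80% power). The printed formula uses Z at α/2 and divides by the square of δ minus the absolute difference in rates. The stated result is 32 per group, raised to about 35 for 10% dropout.

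The Aims in the abstract and the end of the Introduction both state the goal as superiority of the combined treatment over single treatments. Section 2.7.1 names MoCA as the primary outcome. Section 2.11 (Data Analysis) says "One‐way analysis of variance (ANOVA) will be used for comparisons among multiple groups" for normally distributed continuous data, with Kruskal–Wallis otherwise, at one-tailed 0.05. It names no margin.

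**The concern.** In a superiority trial with boundary δ, the hypothesis to be shown is p1 − p2 > δ. With δ = 0.15 and an assumed difference of 0.10, the scenario on which the trial is planned belongs to the null hypothesis. The formula does not reveal this, because δ − |p1 − p2| is squared and the wrong sign disappears. It returns a finite n for a power that no n can deliver.

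This paragraph is the article's only justification for 35 per group. If it does not support the superiority aim, a reader who relies on the 80% figure will misjudge what a positive or a null result means. The hypothesis behind the sample size is also not the one section 2.11 tests, since that section compares groups without a margin and on a different kind of outcome.

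**Working it through.** **Inputs, all from section 2.1.** p1 = 0.90, p2 = 0.80, δ = 0.15, α = 0.025, β = 0.20, 1:1 allocation.

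Variance term: 0.90 × 0.10 + 0.80 × 0.20 = 0.25. Z for 80% power: 0.842. Z for α: 2.241 if 0.025 is two-tailed, as the formula and text literally say, or 1.960 if 0.025 is one-sided.

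**1. Can the stated 32 be reproduced?**

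| Denominator | Z = 1.960 | Z = 2.241 |
|---|---|---|
| As printed, (0.15 − 0.10)² = 0.0025 | (2.802)² × 0.25 / 0.0025 = 784.9 → 785 | (3.083)² × 0.25 / 0.0025 = 950.5 → 951 |
| Sign reversed, (0.15 + 0.10)² = 0.0625 | (2.802)² × 0.25 / 0.0625 = 31.4 → 32 | (3.083)² × 0.25 / 0.0625 = 38.0 → 39 |
| No boundary, 0.10² = 0.01 | 196.2 → 197 | 237.6 → 238 |

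At one-sided 0.05, the level in section 2.11, the same three rows give 619, 25 and 155. Of the variants tried, only the reversed sign with Z = 1.960 gives 32. That is the formula for showing that treatment is not worse by more than 15 points when it is truly 10 points better. Its power at 32 per group is Φ(0.25/0.0884 − 1.960) = 80.7%.

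**2. Chance of showing superiority by 15 points when the truth is 10 points.**

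Standard error at 32 per group: √(0.25/32) = 0.0884. Standardised distance: (0.10 − 0.15)/0.0884 = −0.566.

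- Z = 1.960: P(Z > 1.960 + 0.566) = 0.58%.
- Z = 2.241: P(Z > 2.241 + 0.566) = 0.25%.

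Exact binomial enumeration with the 1.960 cut-off gives 0.66%. The distance is negative for every n, so in the normal approximation the probability stays below the one-sided error rate whatever the size and cannot reach 80%.

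**3. What 32 per group offers for plain superiority (zero boundary, 90% against 80%).**

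- Two-sided 0.05: Φ(0.10/0.0884 − 1.960) = Φ(−0.829), about 20%.
- Two-sided 0.025: Φ(1.131 − 2.241) = Φ(−1.110), about 13%.
- One-sided 0.05: Φ(1.131 − 1.645) = Φ(−0.514), about 30%.

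For 80% power, the pooled formula with mean rate 0.85 gives:

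- Two-sided 0.05: [1.960√(2 × 0.85 × 0.15) + 0.842√0.25]² / 0.01 = 199 per group.
- Two-sided 0.025: the same with 2.241 gives 242 per group.

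**4. Outcome.** The sizing uses an effective rate; section 2.7.1 names MoCA, and section 2.11 analyses continuous data. The article gives no MoCA standard deviation. In standard-deviation units, one pairwise comparison with 32 per group and 80% power at two-sided 0.05 detects about 2.802 × √(2/32) = 0.70 SD (normal approximation, no multiplicity allowance).

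**The case against.** The strongest reply is that the trial was not really sized on an unreachable superiority boundary. The enrolment figure matches a coherent calculation with the opposite sign, so the error may be only a wrong label or sign in print. The arithmetic of that reply stands: 32 does not come from the printed formula. It does not rescue the paragraph, because no section states a non-inferiority aim and the stated aim is superiority. The match is also only arithmetical, so it does not show what the authors intended.

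A reader might go further and infer that enrolling more patients makes this trial less likely to succeed. The documents do not support that. It is true of a test against a 15-point boundary, but section 2.11 does not plan such a test. It compares groups without a margin, and the power of that comparison rises with n.

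It can also be said that an unseen analysis plan might specify a margin-based contrast. That is possible, so the absence of a margin in 2.11 is weak evidence on its own. The contradiction between boundary, rates and formula lies within section 2.1 and does not depend on it.

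**Conclusion.** The point holds for section 2.1 as printed. The boundary (0.15) exceeds the assumed benefit (0.10), so superiority by that boundary is false at the plan's own rates, and the 80% power claim cannot be met at any size. With 32 per group the chance of success is about 0.6% or 0.25%, depending on whether α = 0.025 is read as one-sided or two-tailed. The printed formula yields 785 or 951 on the same two readings.

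The figure 32 supports only a claim of being no more than 15 points worse. For plain superiority at 90% against 80% it gives roughly 20% power (two-sided 0.05) or 13% (two-sided 0.025). These results assume two independent proportions, the article's own rates and the normal approximation. They describe the sizing statement; they are not a forecast for the MoCA analysis, whose power cannot be computed without a standard deviation.

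**What to change.** State one hypothesis in section 2.1 and carry it into section 2.11, with the same outcome, alpha and sidedness in both (they now read two-tailed 0.025 and one-tailed 0.05).

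- **If superiority is the aim, as stated:** delete δ = 0.15 and the claim that 32 per group gives 80% power. Either report the power the planned size has for 90% against 80% (about 20% at two-sided 0.05 or 13% at two-sided 0.025, with about 199 or 242 per group needed for 80%), or replace the paragraph with the precision or detectable difference for MoCA. The second option is better, since MoCA is the outcome analysed; it needs a stated and sourced standard deviation.
- **If non-inferiority to the drug control is also intended:** name it as a separate objective, justify the margin, and decide it by whether the confidence limit excludes the margin. A non-significant ANOVA does not establish it.

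The cost is rewritten text in 2.1 and 2.11 and a less favourable power statement. The correction requires no extra enrolment; if the sponsor wants 80% power for 90% against 80%, that is a separate decision and would mean several times the planned group size.

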#### Control Group

2.6.1

Given that a considerable proportion of patients will require targeted treatment for underlying conditions such as hypertension, glycemic control, anticoagulation, and lipid regulation, concomitant therapies will be permitted during the study period. Moreover, each patient also underwent cognitive rehabilitation training five days a week with two days of rest for a total of 4 weeks. The standard drug treatment group was the control group. The enrolled patients will receive 5 mg of donepezil hydrochloride per night initially, which is increased to 10 mg per night after 30 days in the absence of any adverse reactions. The total treatment duration is 4 weeks.

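### The sample size rests on one treatment-versus-control contrast, so the stated 80% power is not established for the trial's specific focus, combination versus each monotherapy

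*Protocol article*

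**What the plan says.** The Aims paragraph of the abstract describes an efficacy evaluation of the combination, "with a specific focus on determining the therapeutic superiority of this combined approach over monotherapy interventions". The Introduction repeats this: the trial is to show that the combination "offers superior clinical benefits compared to single‐modality treatments for PSCI". The abstract's Background and the Discussion put the question more broadly and also ask about each treatment on its own.

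Section 2.1 uses the "formula for a superiority trial of two independent sample sizes". Its inputs are "an effective rate of 90% in the treatment group and 80% in the control group", "test boundary value *δ* = 0.15", "significance level *α* = 0.025" and "power *β* = 0.20". The result, 32 per group and about 35 after allowing for 10% dropout, is applied to all six groups. Section 2.1 does not say which arm the 90% belongs to. The control is identified in Section 2.6.1: "The standard drug treatment group was the control group".

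**The concern.** The comparators in the aim are EA alone and HOT alone. The comparator in the sample size is the standard drug arm. The article gives no expected rate for EA or HOT as a comparator of the combination, and no difference or power for combination versus either. Giving 32 per group to every arm does not carry the stated power over to contrasts that were never specified.

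This is more than detail left to a fuller document. The article prints its rates, margin, α, β and formula, and it states its focus twice; the two do not refer to the same comparison.

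What is at stake is how a non-significant combination-versus-monotherapy result is read. With a single β of 0.20 printed for the whole trial, a reader could take such a result as evidence that combining adds nothing, when the plan gives no basis for that inference.

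The point is separate from two others in the same section: the printed formula, and the use of an effective rate when the primary outcome is the MoCA score. Correcting both would leave the comparator unchanged.

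**Working it through.** **Inputs from Section 2.1.** p1 = 0.90, p2 = 0.80, δ = 0.15, β = 0.20 (z = 0.842), 32 per group before dropout.

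**Reproducing the plan's 32.** The variance term is 0.90×0.10 + 0.80×0.20 = 0.25. With z = 1.96, (1.96 + 0.842)² × 0.25 = 1.962.

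- Margin added to the difference: 1.962 / (0.15 + 0.10)² = 31.4, rounded up to 32. This matches the plan. It has the form of a non-inferiority calculation with margin 0.15 and one-sided 0.025.
- Printed formula, margin minus difference: 1.962 / (0.15 − 0.10)² = 785. Taking Z at α/2 with α = 0.025 gives 951. Neither matches.
- Plain superiority on the 10-point difference: 1.962 / 0.10² = 197 (199 with a pooled variance under the null). This does not match.

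**Power for combination versus one monotherapy.** The documents give no monotherapy rate. Two assumptions are needed: the 90% belongs to the combination, and the monotherapy rate p2 lies somewhere from 70% to 87.5%, on both sides of the 80% control rate. With n = 32 and two-sided 0.05 (the critical value that reproduces the plan's figure):

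Power = Φ( (0.90 − p2 + m) / √[(0.09 + p2(1 − p2)) / 32] − 1.96 )

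Here m = 0 is true superiority and m = 0.15 is the margin-added calculation.

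Example at p2 = 0.85: the standard error is √[(0.09 + 0.1275)/32] = 0.0824. With m = 0, 0.05/0.0824 = 0.606 and Φ(0.606 − 1.96) = 0.09. With m = 0.15, 0.20/0.0824 = 2.426 and Φ(2.426 − 1.96) = 0.68.

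| Assumed monotherapy rate | Superiority (m = 0) | Margin added (m = 0.15) |
|---|---|---|
| 70% | 54% | 95% |
| 75% | 36% | 90% |
| 80% | 20% | 81% |
| 82.5% | 14% | 75% |
| 85% | 9% | 68% |
| 87.5% | 5% | 60% |

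Setting m = 0 and solving for about 80% power gives a monotherapy rate of about 62% (power 0.79 at 62%, 0.82 at 61%), which is 18 points below the plan's control rate.

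**Power to beat both monotherapies.** The two contrasts share the combination arm, so they are positively correlated.

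- Both at 80%: about 68% with the margin added; about 7% (normal approximation) to 10% (binomial simulation with a pooled test) for superiority.
- Both at 85%: about 52% with the margin added; about 2% to 3.5% by the same two methods for superiority.

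**The case against.** The strongest reply is that the direction of any power loss cannot be derived from the documents. A reader might infer that the combination-versus-monotherapy gap must be smaller than 10 points because EA and HOT are presented as effective, so that power must fall below 80%. The documents do not support this. The control is an active drug arm with cognitive training, so a monotherapy could work and still equal or fall short of it. The abstract's Background says that standalone efficacy will be evaluated; it does not assume it. At monotherapy rates of 70% or 75%, power is above the 80% reference row in both columns. This objection stands, and it is why the table covers both sides of 80%.

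Three further points also stand. Section 2.1 never says that the 90% is the combination; if it describes a monotherapy, the combination has no assumed rate at all. Combination versus monotherapy is the specific focus but not the only aim, and treatment versus control is a legitimate contrast for the broader question. A reader might also infer that the article claims 80% power for combination versus monotherapy; it makes no such claim.

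It can be added that true-superiority power is only about 20% even at 90% versus 80%, so the margin problem dominates. That is fair as to size, but repairing the margin would not supply an assumption for the contrasts of interest.

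**Conclusion.** The point holds in this form: the sizing contrast is an unnamed treatment arm versus the standard drug arm, the specific focus is combination versus EA and versus HOT, and the stated 80% power is not established for that focus. This follows from the text and needs no assumed rate.

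The size does depend on assumptions: the combination at 90%, 32 evaluable per group, two-sided 0.05, and a monotherapy rate the documents do not give. Over 70% to 87.5%, power per contrast runs from 54% down to 5% for superiority and from 95% down to 60% with the margin added. Relative to the plan's reference, it falls if the monotherapies exceed the control rate and rises if they fall short. For the superiority question as worded, it reaches about 80% only if the monotherapy rate is about 62% or lower. The documents do not support saying that power must fall, or that the sizing contradicts a premise of the trial.

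**What to change.** In Section 2.1, say which arms the 90% and the 80% refer to. Then take one of two routes.

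1. State an assumed monotherapy value on the scale of the primary outcome (MoCA), and replace the 80% with the power that 32 evaluable per group gives for combination versus EA and for combination versus HOT. As a guide, 32 per group at two-sided 0.05 gives 80% power for a standardised difference of about 0.70, 52% for 0.5 and 22% for 0.3.
2. If no such value can be supported, state that the size was set for treatment versus control only and that the trial is not powered for combination versus monotherapy. Report those contrasts as differences with confidence intervals, and state that a non-significant result will not be read as no added benefit.

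The Aims should be worded to match. The cost is a few sentences and a less favourable stated power. Enrolment and procedures do not change, and no extra patients are needed.
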